### Study Design: Stepped-Wedge Randomized Design

The stepped-wedge cluster-randomized design was chosen for this trial because of its clear methodological benefits. Unlike parallel designs, all clusters eventually receive intervention, enhancing acceptability in clinical settings where prior evidence suggests potential benefit [28,29]. The phased implementation also mirrors real-world logistical constraints while allowing for both within- and between-cluster comparisons, thereby improving statistical efficiency and power [28,30]. Additionally, repeated measurements over time enable adjustment for secular trends, strengthening causal inference [28-31]. These characteristics make the stepped-wedge design especially suitable for pragmatic evaluations of health care interventions.

This nationwide, multicenter, stepped-wedge cluster-randomized trial (SW-CRT) follows the CONSORT-AI (Consolidated Standards of Reporting Trials-Artificial Intelligence) and SPIRIT-AI (Standard Protocol Items: Recommendations for Interventional Trials-Artificial Intelligence) guidelines [32,33]. It will evaluate whether AI can improve CXR interpretation in routine clinical care across Brazil. Cities will act as clusters, comprising public, private, and philanthropic health care units to ensure broad socioeconomic and geographic representation [28,30,31,34]. All clusters will begin in the control condition (standard physician interpretation) and will cross over to the intervention (AI-assisted physician interpretation) at randomly assigned monthly intervals. Potential contamination across clusters will be minimized by selecting independent clinical units with nonoverlapping staff and workflows.

A batched stepped-wedge approach allows staggered initiation, accommodating operational constraints while minimizing contamination or learning effects. Once a cluster transitions, it remains in the intervention arm (Figure 2). Simple urn-based randomization without replacement will occur independently in each batch. Participating centers within cities must have infrastructure for CXR interpretation (negatoscope or digital screen), reliable internet access, and commitment to study protocols.

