### Statistical Analysis

The sample size was calculated to detect a minimum difference of 10% in the primary outcome—a binary indicator of whether the physician correctly labeled a CXR—between the AI-assisted and control groups. The calculation accounted for the stepped-wedge cluster-randomized design with batched implementation using the following assumptions: 9 clusters randomized in 3 batches to cross over from control to intervention, 10 time periods, a baseline detection rate of 67% in the control group, an expected increase to 77% in the intervention group, and an intracluster correlation coefficient ranging from 0.001 to 0.003.

The design effect was adjusted for the correlation structure induced by repeated measures within clusters over time using methods described by Hussey and Hughes [28] and extended to account for batched randomization, as described by Hemming et al [35,36]. The power calculation targeted 80% power at a 2-sided significance level of 5% and accounted for potential variability in cluster sizes. The final average cluster size was 37, and the overall sample size was inflated by 10% to account for anticipated exclusions due to image quality issues or missing data (dropout). This approach ensures adequate power to detect a meaningful effect of the intervention while maintaining the integrity of the stepped-wedge design with staggered implementation across batches.

Primary analysis will follow the modified intention-to-treat principle. All eligible CXRs (the unit of analysis in this study) will be analyzed according to the study group (control or intervention), to which their corresponding cluster was allocated at the time of image acquisition, regardless of physician adherence to the intervention or exposure to AI output. Images of poor quality, as defined by our radiologists, will be excluded postrandomization.

The primary outcome analysis will use a generalized linear mixed model with a binomial distribution and logit link function to estimate the effect of the AI-assisted intervention on detection probability. The model will include fixed effects for the intervention group (AI-assisted vs control), calendar time (to adjust for secular trends), time since intervention rollout (to account for learning or adaptation effects), and batch effects. In addition, random intercepts for clusters will be specified to account for intracluster correlation.

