Results will be reported as adjusted odds ratios with 95% CIs and 2-sided *P* values. Model fit and assumptions will be evaluated using the Residual Diagnostics for Hierarchical (Multilevel/Mixed) Regression Models (DHARMa) [37]. In case of convergence issues or model instability, generalized estimating equations with robust SEs will be used as an alternative to estimate population-averaged effects. Independent models will also be fitted for each radiological finding, as well as for the pulmonary abnormality and TB algorithm.

Model performance metrics will be reported with 95% CIs [38,39]. Responses to questions regarding the mobile interface will be summarized as frequencies. Chi-square test and ordinal logistical regression will be used to investigate associations between these responses and physician characteristics (eg, years in practice and biological sex). Additionally, generalized linear mixed models will be fitted with the algorithm’s output as the dependent variable, adjusted for image characteristics, to investigate their effect on AI classification.

Missing data are expected to be minimal due to app-enforced completeness checks. Incomplete records will be described, and sensitivity analyses using multiple imputation will be performed if the proportion of missing data exceeds 10%. All analyses will be performed in R (R Foundation for Statistical Computing), and code scripts will be version-controlled and archived to ensure reproducibility.

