## Results

The LuAna trial received institutional ethics board approval and was formally activated in October 2024. Data collection began in January 2026 with a projected end date of September 2026. At interim review (November 2025), 3 of the 13 participating centers had completed all site activation requirements and were prepared to initiate enrollment. The trial is currently ongoing with active data collection. Data analysis is scheduled for completion by November 2026, and results dissemination is expected by January 2027.

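### With nine cities, the robust-SE GEE fallback needs a small-sample correction to hold the 5% level, and the city-intercept GLMM holds it only while the reader mix within a city stays stable

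*Protocol article*

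**What the plan says.** The Study Design section defines the cluster: "Cities will act as clusters, comprising public, private, and philanthropic health care units". The Statistical Analysis section plans "9 clusters randomized in 3 batches to cross over from control to intervention", over "10 time periods", with "a baseline detection rate of 67% in the control group" and "an intracluster correlation coefficient ranging from 0.001 to 0.003". The Results section shows that centers outnumber cities: "3 of the 13 participating centers had completed all site activation requirements".

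The primary model in Statistical Analysis is a logistic GLMM. Its fixed effects are treatment, calendar time, time since rollout and batch. One random term is named: "random intercepts for clusters will be specified to account for intracluster correlation". If the model fails to converge or is unstable, "generalized estimating equations with robust SEs will be used as an alternative to estimate population-averaged effects". The article names no center, physician or city-by-period effect, no degrees-of-freedom method, and no variant of the robust SE. The SAP is not shown.

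**The concern.** Two features affect the standard error of the primary result.

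**Few clusters.** A sandwich SE is estimated from between-cluster variation in residuals. With nine clusters it is biased downward and itself noisy, so comparison with the normal distribution rejects too often. The fallback is meant for unstable fits. With nine clusters and a planned ICC near zero, a variance estimate on the boundary is a plausible trigger.

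**Readers inside cities.** The outcome is whether a physician read a film correctly, and several centers and readers sit within a city. The document itself expects readers to differ and to change. The Introduction names variable reader skill as a limit of chest radiography, and the Physicians section sets no limits on experience or imaging training. Textbox 1 plans to study change in physician performance over time. A city intercept absorbs only what is constant in a city. If the reader mix shifts between months, that shift is counted as independent film-level noise.

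At stake are the confidence interval and P value of the primary comparison.

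**Working it through.** **Inputs from Statistical Analysis:** 9 cities in 3 batches, 10 periods, control rate 67%, intervention rate 77%, ICC 0.001-0.003, average cluster size 37, 80% power, two-sided 5%.

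**Assumptions:** 37 is read as films per city-period, because the text does not say. The batch layout is in a figure not shown, so several layouts were tried.

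**1. The plan's own figure.** The Hussey-Hughes variance with period and batch effects gives about 72% to 99% power, depending on layout. With 6 periods per batch and starts 2 periods apart (9 x 6 x 37 = 1998 films), power is 83% at ICC 0.001 and 81% at ICC 0.003. The stated 80% is therefore compatible with 37 per city-period. With 37 films per city in total, power would be only about 22-28%.

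**2. False-positive rate at the planned ICC.** Null data were binomial at 67%. The GLMM used a city intercept and a Wald z test. GEE used independence (ind.) or exchangeable (exch.) working correlation, with an uncorrected sandwich SE and z test. Kauermann-Carroll (KC) and Mancl-DeRouen (MD) SEs were referred to t with 9 - 2 = 7 degrees of freedom. CAC is the cluster autocorrelation; 1.0 means no decay. ICC is 0.003 throughout. Rows with CAC 1.0 have 2000 replicates and rows with CAC 0.8 have 1500.

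| Layout | CAC | GLMM | GEE ind. | GEE exch. | KC, t(7) | MD, t(7) |
|---|---|---|---|---|---|---|
| 9 cities x 10 periods | 1.0 | 4.8% | 12.8% | 13.4% | 4.1% | 2.2% |
| Staggered batches A | 1.0 | 5.6% | 13.8% | 14.8% | 5.4% | 3.0% |
| Staggered batches B | 1.0 | 5.6% | 19.2% | 20.0% | 5.0% | 1.3% |
| 9 cities x 10 periods | 0.8 | 6.1% | 13.0% | 14.0% | 4.5% | 2.3% |
| Staggered batches A | 0.8 | 6.4% | 15.3% | 15.6% | 6.1% | 2.5% |
| Staggered batches B | 0.8 | 7.1% | 20.7% | 21.3% | 6.3% | 2.0% |

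Monte Carlo error near 5% is 1.96 x sqrt(0.05 x 0.95 / 2000), about 1 point.

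The GEE inflation does not depend on how 37 is read. With 3.7 films per city-period it is 15.0% and 16.6%, with the GLMM at 4.9%. Nor does it depend on categorical months. With linear time and no time-since-rollout term, at ICC 0.003 and CAC 0.8, it is 12.0% and 12.1%. Across all scenarios run, including larger ICCs, it is about 10-21%.

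**3. City-intercept GLMM when correlation decays.** These ICC and CAC values are assumed; the document does not give them.

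| ICC | CAC | False-positive rate |
|---|---|---|
| 0.01 | 0.8 | 6-9% |
| 0.03 | 0.8 | 7-11% |
| 0.05 | 0.8 | 8-11% |
| 0.05 | 0.5 | 14-17% |
| 0.1 | 0.8 | 12-14% |
| 0.1 | 0.5 | 23-27% |

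**4. City-intercept GLMM with explicit readers.** City ICC is near the planned value, there are 37 films per city-month, and the time-since-rollout term is omitted. Physician ICC, number of readers, workload and turnover are all assumed.

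- No reader effect: about 5.4-6.2%.
- Four stable readers sharing films equally: 6.1-6.3% at physician ICC 0.05, 6.3-6.6% at 0.10.
- Randomly varying workloads, ICC 0.10: 6.5-9.2%.
- 10% monthly turnover, ICC 0.05: 7.2-8.7%.
- Three readers, 30% monthly turnover, ICC 0.10: 10.5-15.8%.
- A separate set with uneven reader shares: 6-8% (staggered, 6 periods) and 11-14% (10 periods) at ICC 0.05; 9-15% and 15-23% at ICC 0.10.

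The inflation comes from a shifting or uneven reader mix. Many films per reader is not enough by itself.

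**5. After correction.** Over all scenarios run, GEE with KC and t(7) gives about 4-8%, and with MD and t(7) about 1-4%. The GLMM with an added city-by-period effect gives about 7-12% with z and about 2-6% with t(7). The extra random effect alone is therefore not enough; the reference distribution must change too.

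**The case against.** The strongest objection is that the article never says the robust SEs will be uncorrected. It is a condensed text, the SAP is not shown, and a small-sample variance method is the kind of detail a SAP carries. The fallback is also contingent, and residual diagnostics are planned for the mixed model. This stands to the extent that the point must be conditional: the 10-21% applies if a standard sandwich SE and z test are used. It does not remove the point. The article fixes a method by name for a nine-cluster trial, and in its usual form that method does not hold its level.

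A reader might infer more in four places, and the documents do not support it.

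- **That the primary GLMM has a false-positive rate of 7-20%.** At the planned ICC it is about 5-7%. Higher rates need reader differences together with turnover or uneven workload, or a larger ICC with decay. The article gives no physician ICC, roster size or turnover rate.
- **That the fallback fails because a sandwich matrix from nine clusters cannot have full rank.** The primary test concerns one coefficient, and the coding of calendar time is not stated. The problem is few-cluster bias, not rank.
- **That power is lower than claimed because the true ICC is larger.** That rests on ICCs the document does not contain.
- **That a particular number of permutations is available.** That depends on the layout in the figure not shown.

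**Conclusion.** The point holds in conditional form. With a standard sandwich SE and z test, the GEE fallback has a false-positive rate of about 10-21% instead of 5%. This needs no assumption about readers and appears at the planned ICC without decay (about 12-20%).

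The primary GLMM is close to nominal, about 5-7%, at the planned ICC. It is not protected against a changing reader mix or decaying correlation. Under an assumed physician ICC of 0.05-0.10 with turnover or uneven workload the rate is roughly 6-20%, and the most unfavourable runs slightly exceed this. With stable, equally shared reading it is about 6-7%. The direction follows from a model the article states. The size rests on assumed values, so the range should not be quoted as the error rate of the planned primary analysis.

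**What to change.** **GEE fallback.** Specify a bias-corrected sandwich SE, Kauermann-Carroll or Mancl-DeRouen, with t degrees of freedom based on nine clusters (9 - 2 = 7). In these simulations Mancl-DeRouen was conservative and Kauermann-Carroll closer to 5%. Choose one in advance.

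**Primary GLMM.** Add a city-by-period random effect, and a physician random intercept where it can be estimated, with small-sample t-based inference. Physicians log in with personal credentials and data are logged automatically (Data Collection), so a reader identifier should be available.

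**Optional sensitivity analysis.** Report a within-batch permutation P value, with the number of allocations taken from the actual layout.

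**Cost.** Analysis code and SAP wording, before the analysis due by November 2026. The 97.5% point of t(7) is 2.365 against 1.960, so the reference distribution alone widens intervals by 2.365 / 1.960 = 1.21, about 21%, and power falls somewhat. Richer random effects raise the chance of singular fits with nine cities. State in advance which simpler model follows a singular fit, so that it does not lead straight to an uncorrected GEE.

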## Methods

### Algorithm Development

#### Overview

Between 2019 and 2024, 3 independent deep-learning models were developed and internally validated [22]. The “Lung Abnormality” model classified CXRs as either normal or abnormal. The “Radiological Findings” model categorized patterns into predefined classes, including consolidation, pulmonary opacity, pneumothorax, atelectasis, pleural effusion, and cardiomegaly. Finally, the “Tuberculosis” model predicted whether a CXR was suggestive or not suggestive of pulmonary TB. The models were trained on CXRs from adults aged 18 years or older, including both male and female patients. The dataset comprised anteroposterior or posteroanterior views sourced from public databases and from multiple partner health care centers across Brazil, including referral clinics for TB care.

Model predictions were given as probabilities ranging from 0 to 1, with a threshold of 0.5: values of 0.5 or higher were classified as positive, and values below 0.5 as negative. The exceptions are pneumothorax (0.8), consolidation (0.6), and TB (0.4), which had different thresholds determined by the GHOST (generalized threshold shifting) method [23]. Heatmaps highlight regions of interest, contributing to the algorithm’s output (Figure 1).

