#### External Algorithm Validation

An external retrospective validation of 1092 anonymized CXRs, including 586 double-read by thoracic radiologists at Hospital Israelita Albert Einstein, demonstrated variability in model performance. The Pulmonary Abnormality and Tuberculosis models achieved AUC values of 0.89 and 0.84, respectively, whereas the Radiological Findings model showed AUC values ranging from 0.811 to 0.96, as shown in Table 2.

**Table 2. T2:** External validation dataset values.

Model	AUC^a^	Sensitivity	Specificity	Accuracy
Pulmonary abnormality	0.89	0.82	0.84	0.82
Tuberculosis	0.84	0.83	0.71	0.77
Radiological findings				
Consolidation	0.92	0.95	0.70	0.74
Lung opacity	0.91	0.90	0.72	0.80
Atelectasis	0.81	0.55	0.87	0.81
Cardiomegaly	0.95	0.84	0.90	0.90
Pneumothorax	0.96	1.0	0.79	0.80
Pleural effusion	0.95	0.80	0.92	0.90

a AUC: area under the receiver operating characteristic curve.

In the prospective phase of the Radiological Findings model, which included 30 real-time cases, no statistically significant differences were observed. All physicians were provided with standardized CARPL (Clinical AI Research Platform for Labeling) training to promote uniformity in image labeling [24].

Therefore, the current gap between internal and external performance per class of the Radiological Findings model underscores the need for multi-institutional datasets and rigorous real-world testing before clinical adoption. The AI models will be locked for the duration of the trial; no updates to weights or thresholds will be implemented once recruitment starts. Overall, this study underscores both the potential and limitations of AI in radiology, reinforcing that limited real-world evidence warrants caution and that robust validation frameworks are as essential as algorithm development [25-27].

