#### Exclusion Criteria

CXRs performed for peripherally inserted central catheter line positioning, preoperative risk assessment, lung cancer screening, or trauma-related evaluation will be excluded. In addition, radiographs printed on plain paper and examinations with technical quality below the minimum acceptable standard will also be excluded.

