**Figure 3. F3:**
[figure not shown]
Workflow for chest X-ray (CXR) interpretation in control and intervention groups. Top panel (control group—without AI): CXRs from patients with respiratory complaints are interpreted solely by the physician (1), without access to AI support (2). Bottom panel (intervention group—with AI): physicians first perform an initial assessment of the CXR (1) and register their findings via the LuAna mobile app (2). After this, the AI model processes the image and returns a score and a heatmap highlighting abnormal regions (3). The physician can then review and, if needed, revise their interpretation based on the AI output (4). Both pre- and post-AI interpretations are recorded for analysis. For both groups, CXR assessments are compared against a reference standard, defined as thoracic radiologist evaluation performed on the CARPL, with reports independently double-validated by thoracic radiologists blinded to both the physician assessment and AI output. The primary outcome is the comparison of radiologic findings detection rates before and after AI assistance relative to the reference standard. The workflow includes data acquisition at the study centers, followed by radiologist annotation, primary and secondary end point evaluation, and statistical analysis at the coordinating center. AI: artificial intelligence; CARPL: Clinical Artificial Intelligence Research Platform for Labeling.

Only demographic variables, including age group, sex, and race, will be collected in aggregated form to characterize the study population and allow for fairness analyses, ensuring equitable and unbiased AI performance. CXRs will be captured either by photographing printed films positioned on a lit negatoscope, by photographing digital images displayed on a picture archiving and communication system monitor, or by direct screen capture, all following strict protocols to guarantee full anonymization. Physicians will capture only the thoracic image, ensuring that all patient identifiers are systematically removed and never visible. A patient ID entered solely to return the radiologist’s report to the local health unit will be encrypted and remain inaccessible to the research team. Nondiagnostic images or studies failing predefined quality-control criteria will be excluded from analysis.

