### Reference Standard Generation, Report Return, and Critical Findings

The radiologists are responsible for producing the ground-truth (reference standard) for all CXR images during the study. The first step in ground-truth generation is to assign 2 thoracic radiologists to independently interpret the CXR images to set up the reference standard, classifying each finding as “normal” or “abnormal.” The correct classification matches the reference standard. For cases classified as *abnormal*, the presence or absence of the relevant radiological findings (consolidation, pulmonary opacity, pneumothorax, atelectasis, pleural effusion, and cardiomegaly) will be assessed, as well as the presence or absence of changes suggestive of TB. Based on these evaluations by the 2 thoracic radiologists, the ground truth is established. The radiologists will be blinded to both the physicians’ interpretations and the AI outputs.

A chest radiograph will be labeled as suggestive of pulmonary TB if at least 1 radiographic feature considered compatible with pulmonary TB is present, as determined by the adjudicated thoracic radiologist reference standard. Examples include cavitation, upper-lobe–predominant consolidation or opacities, fibronodular changes or scarring with upper lobe volume loss, or a miliary pattern. If none of these features is present, the examination will be labeled as “not suggestive of pulmonary TB.”

For physician performance analyses, an examination will be considered correctly classified when the physician’s binary classification (normal vs abnormal; suggestive vs not suggestive of pulmonary TB; presence or absence of specific radiographic patterns) matches the adjudicated thoracic radiologist reference standard. In cases of any disagreement between the 2 experts in any of the evaluated items, a third radiologist, more senior, will adjudicate.

All findings will be registered in the CARPL, with abnormalities annotated to allow direct comparison with AI outputs. This will serve as the reference value for model validation and performance analysis (Figure 4).

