## Discussion

### Principal Findings

This trial is a pivotal effort to evaluate how AI can enhance diagnostic accuracy, clinical workflows, and physician performance in interpreting chest radiographs.

By using a batched stepped-wedge cluster-randomized design across a nationally representative sample of health care settings, we aim to rigorously assess the real-world utility of LuAna, an AI-powered platform for CXR interpretation developed in the public sector to assist general practitioners.

Despite ongoing debate about the advantages of SW-CRTs, including concerns about equipoise and delayed access to interventions [41], this design offers distinct benefits for implementation research. Governed by the same ethical principles as all clinical research [42], SW-CRTs are particularly valuable when evaluating innovations that are expected to be beneficial and for which withholding access may be contentious [42]. In the SUS context, this approach ensures that all centers ultimately gain access to AI support, promotes fairness and acceptability, and provides a pragmatic pathway to sustainable integration of the intervention into routine care.

The central goal is to determine whether LuAna improves clinicians’ ability to detect radiographic abnormalities, particularly in environments with limited access to radiology expertise. Comparisons against adjudicated, double-blinded radiologist interpretations will enable the quantification of diagnostic agreement, while stratified analyses by site type and physician characteristics will offer insights into contextual factors that may influence AI performance.

Importantly, the trial also investigates the clinical impact beyond diagnostic accuracy. By evaluating patient management decisions and turnaround times, we aim to capture how AI affects treatment pathways and efficiency in routine care. Usability assessments will provide critical feedback for refining and scaling the platform, thereby ensuring seamless integration into diverse clinical workflows across both mobile and desktop interfaces.

Robustness will be evaluated through sensitivity analyses on image quality, artifacts, and medical devices, thereby validating the model’s generalizability under real-world conditions. Additionally, longitudinal analysis of physician interpretations will explore whether repeated AI exposure improves independent performance, highlighting AI’s potential educational role.

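### The secondary analysis of external factors models the AI's output without conditioning on the reference standard, so it cannot tell an effect on AI accuracy from a difference in disease prevalence

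*Protocol article*

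**What the plan says.** The Statistical Analysis section describes generalized linear mixed models with the algorithm's "output as the dependent variable, adjusted for image characteristics, to investigate their effect on AI classification". Textbox 1 under Secondary Outcomes defines the matching outcome in the same terms: the association of AI outputs with radiologist-labelled features of the film (quality of the photograph, thoracic devices, technical artifacts). Neither place puts the reference standard into this analysis. AI performance against the reference standard is a separate secondary outcome and is not stated by image characteristic.

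The output is a score that is then dichotomized: "Model predictions were given as probabilities ranging from 0 to 1, with a threshold of 0.5", with other cut-offs for some findings. The Discussion says how results on these factors will be read: "Robustness will be evaluated through sensitivity analyses on image quality, artifacts, and medical devices".

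The missing term will be available. Under Reference Standard Generation: "The radiologists are responsible for producing the ground-truth (reference standard) for all CXR images during the study".

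Poor images are removed in three places. Exclusion Criteria: "examinations with technical quality below the minimum acceptable standard will also be excluded". Data Collection: "Nondiagnostic images or studies failing predefined quality-control criteria will be excluded from analysis". Statistical Analysis: "Images of poor quality, as defined by our radiologists, will be excluded postrandomization".

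**The concern.** A working AI should give more positive outputs where there is more disease. If films with a given characteristic also contain the finding more often, the output will be associated with that characteristic even when the AI errs at the same rates in both groups. The model as described has no term to absorb this.

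The opposite failure is also possible. A characteristic that causes both more missed findings and more false alarms can leave the overall proportion of positive outputs unchanged. The coefficient is then null although performance has deteriorated.

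At stake is the secondary objective on external influences and the robustness statement that the Discussion attaches to these factors. A reader could be told that devices distort the AI when they do not, or that they are harmless when they are not.

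The photo-quality factor has a second, separate limitation. With the poorest images removed, its effect is estimated over a shortened range.

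**Working it through.** The plan gives no figure for this analysis, so there is none to reproduce. The check asks what the described model returns when the truth is known.

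**Inputs**
- Sensitivity (Se) and specificity (Sp) from Table 2, external validation. The pleural effusion row reads "Pleural effusion 0.95 0.80 0.92 0.90" (AUC, sensitivity, specificity, accuracy). Lung opacity has Se 0.90 and Sp 0.72.
- Prevalence of the finding with and without the characteristic: **assumed**. For orientation, the pleural effusion row implies an overall prevalence of (0.90 − 0.92)/(0.80 − 0.92) = 0.17, which is rough because the inputs are rounded.
- Clustering is ignored; it does not alter the mechanism.

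**Formula.** P(AI positive) = Se × prev + (1 − Sp) × (1 − prev). The odds ratio (OR) compares films with and without the characteristic.

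**1. Pleural effusion, accuracy identical in both groups**
- Prevalence 10%: 0.080 + 0.072 = 0.152
- Prevalence 15%: 0.120 + 0.068 = 0.188
- Prevalence 25%: 0.200 + 0.060 = 0.260
- Prevalence 40%: 0.320 + 0.048 = 0.368
- Prevalence 50%: 0.400 + 0.040 = 0.440

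| Prevalence without vs with | P(AI positive) | OR from the planned model |
|---|---|---|
| 15% vs 15% | 0.188 vs 0.188 | 1.00 |
| 15% vs 25% | 0.188 vs 0.260 | 1.52 |
| 15% vs 40% | 0.188 vs 0.368 | 2.51 |
| 10% vs 50% | 0.152 vs 0.440 | 4.38 |

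The last row is (0.440/0.560)/(0.152/0.848). The correct answer for an effect on accuracy is 1.00 in every row. Across the six radiological findings and TB in Table 2, the ranges are 1.25 to 1.52 (15% vs 25%), 1.74 to 2.51 (15% vs 40%) and 2.43 to 4.38 (10% vs 50%). TB is lowest and pleural effusion highest each time.

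**2. Real degradation hidden at equal prevalence.** Lung opacity, prevalence 40% in both groups, Se falling from 0.90 to 0.75 and Sp from 0.72 to 0.62 (the falls are assumed):
- Before: 0.90 × 0.40 + 0.28 × 0.60 = 0.528
- After: 0.75 × 0.40 + 0.38 × 0.60 = 0.528

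OR = 1.00.

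**3. Real effect masked by prevalence.** Pleural effusion, Sp falling from 0.92 to 0.82, prevalence 25% without and 12% with the characteristic (assumed):
- Without: 0.80 × 0.25 + 0.08 × 0.75 = 0.260
- With: 0.80 × 0.12 + 0.18 × 0.88 = 0.254

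The planned model gives OR 0.97. The true OR for a false positive is (0.18/0.82)/(0.08/0.92) = 2.52.

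**4. Which change repairs it.** 200,000 simulated films, pleural effusion, 15% vs 40%, accuracy identical in both groups:

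| Model | OR for the characteristic |
|---|---|
| Output on characteristic | 2.50 |
| Error on characteristic | 1.33 |
| Output on characteristic and reference status | 0.99 |
| Error on characteristic and reference status | 0.98 |

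Switching to error alone leaves a bias, because Se and Sp differ and the mix of the two error types changes with prevalence. By hand, the error rates are 0.20 × 0.15 + 0.08 × 0.85 = 0.098 and 0.20 × 0.40 + 0.08 × 0.60 = 0.128, an OR of 1.35. Conditioning on reference status removes it.

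**The case against.** **The sentence is brief and the article is condensed.** A full covariate list may stand in a document not shown, and nothing excludes reference status. This carries some weight. However, the article names both the dependent variable and the explanatory factors, and Textbox 1 repeats that pairing as the outcome definition. That is a stated method, not a detail left open.

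**The plan is internally consistent.** The objective concerns predictions, the outcome concerns outputs, and the model matches both; the robustness reading comes from the Discussion, which does not fix the form of its sensitivity analyses. This is true, and as a description of when the AI says positive the model is sound. It does not support a statement about accuracy or robustness. Using the continuous score instead of the dichotomized call does not help, since scores also rise with disease.

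**The size is hypothetical.** This stands. A reader might infer that prevalence will be reported as an image effect. The documents do not support that: they give no prevalence by device, artifact or photo quality, and at equal prevalence the spurious OR is 1.00. The link is plausible mainly for devices and less obvious for photo quality, which depends partly on how the film or screen was captured. The offsetting problem in step 2, by contrast, needs no prevalence difference.

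**The quality exclusion is defensible.** A reader might also infer that dropping poor images produces the prevalence confounding. It does not; it only shortens the quality range. Acceptable images are a reasonable intended-use target, some of the restriction is set by eligibility, and the exclusion in Statistical Analysis stands in the primary-analysis paragraph. The Data Collection exclusion, though, is not limited to the primary analysis.

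**Conclusion.** The point holds for a secondary analysis. As described, the external-factors model cannot separate an effect on AI accuracy from a difference in prevalence, and it can miss offsetting losses of sensitivity and specificity.

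With the pleural effusion values, the spurious odds ratio runs from 1.0 (equal prevalence) through 1.5 and 2.5 to 4.4 (10% vs 50%). These sizes rest on assumed prevalences and on accuracy being the same with and without the characteristic. The existence of the problem does not rest on any particular prevalence.

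The truncated range of photo quality is a separate and smaller matter of what the result can be said to cover. The primary comparison of physicians with and without AI, its sample size and the randomization are untouched.

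**What to change.** Restate the model in Statistical Analysis and the outcome in Textbox 1 so that both condition on the reference standard. Either:
- model AI correctness separately in reference-positive films (sensitivity) and reference-negative films (specificity), with the image characteristics as explanatory terms; or
- keep the output as dependent variable and add reference status and its interaction with each characteristic.

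Modelling error without reference status is not enough.

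The cost is a changed model statement. Reference labels and image labels are already planned, so no new data are needed. The downside is lower precision within each stratum, chiefly among reference-positive films for rare findings. Pneumothorax is the likely problem: its Table 2 row implies a prevalence of about (0.80 − 0.79)/(1.00 − 0.79) = 0.05, and its sensitivity of 1.0 leaves little or no error to model. Report estimates and intervals there without relying on tests.

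For photo quality, either state that the effect applies only to images of acceptable quality, or keep in this one analysis any collected image that received a reference label. The first costs one sentence. The second need not change eligibility if it is confined to images already collected, but the Data Collection exclusion would have to be worded to allow it.
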